### Health Care and DTs

A DT is a virtual representation of a physical object that is used to simulate a process. This simulation can be used to predict the impact of a new process or to modify an existing process to improve risk identification and clinical efficiency. It has the potential to contribute to real-time decision-making to effectively predict outcomes and to make cost-reduction improvements. Because of these attributes, a DT with virtual representations has been shown to have widespread use in industry to simulate the impact of proposed modifications and run “what-if” scenarios before implementation. When a modification is introduced, DTs can be continuously updated with performance data that can be used to manage the process in real time. This real-time monitoring in parallel with the updating of a DT leads to improved management and system stability while enhancing system security [68,69].

### Health Care Simulation

Simulation in health care has long been used in training and in improving outcomes in areas such as diagnosing cardiorespiratory arrest, designing mental health treatments, and, most recently, planning treatment interventions such as surgery. The major drawback of simulations is that they are fixed; they do not receive new data, and they are generally not easily modifiable when clinical situations change [70-72]. DTs differ significantly from simulations because of the continuous flow of data from the patient to the DT, which can lead to modification of the DT in real time by simulating the patient’s clinical course [73]. When used in health care, a DT is a virtual representation of a patient. A health care DT has essentially the same attributes as an industrial DT. A patient DT is constructed by analyzing relevant characteristics and problems of that individual through AI to simulate the potential treatment options and provide the best clinical course. DTs have the potential to improve treatment compliance, address individual risks, reduce barriers to improvement, intervene before side effects become problematic, and enhance a therapeutic alliance between the patient and provider. This approach of combining individual characteristics and AI data from a DT that is unique to a patient helps to support the goal of personalized medicine. The health care DT represents a key technology that brings together the advantages of a comprehensive picture of a patient, leading to a precise diagnosis and a personalized treatment plan that is evidence-based yet still personalized to that individual [74,75]. As treatment progresses, the DT is continuously updated by monitoring the patient’s progress through data collection and providing feedback to the patient and treating provider. The changing clinical picture leads to a modification of that patient’s DT.

### Treatment Trajectory

Treatment trajectories leading to clinical improvement rarely follow straight linear paths toward a goal [76]. Figure 2 illustrates this for a hypothetical patient. As noted in the figure, the delta of change over a course of treatment can vary. These changes could lead to different approaches or consideration of different treatment options. Ongoing tracking data from the patient and revision of the patient’s DT, as these data become available, modify the DT and can help identify these deltas. This process can provide new insights and a change in clinical decision-making. This back-and-forth data exchange in real time between the patient and that person’s DT can be key to providing personalized medicine.

**Figure 2. F2:**
[figure not shown]
Hypothetical treatment course.

### Designing and Developing a DT for NCDs

To our knowledge, a protocol designed to assess the use of a DT to treat NCDs has not been conducted or reported in scientific literature. As noted above, NCDs are lifestyle diseases that can require a multidisciplinary approach toward effective diagnosis and behavior change to impact the long-term reversal of health risk factors using a biopsychosocial approach. The interdisciplinary approach needed to effectively treat a patient with an NCD requires the following:

Comprehensive medical review and treatment of the consequences of the NCD.Biopsychosocial evaluation with risk assessment that can impact treatment goals.Psychological assessment and comprehensive treatment when needed.Modification of behaviors that have led to the development of the NCD.Evaluation of current activity, presence, and/or treatment of pain, and integrated rehabilitation when identified.

The design and implementation of a DT for an NCD is as follows:

Conduct a literature review of appropriately designed studies related to any particular NCD. These studies will provide an analysis of health risks and therapeutic clinical trials that include both health risks and responder analyses. This information will be used through supportive AI decision-making to form a DT and to offer clinical support.Obtain a patient-centered interface that connects with an electronic medical record to collect existing data. This will allow for the assessment of the patient’s baseline key health indicators, to track key variables to be used to update the patient’s DT while providing feedback, including contextually specific motivational messaging, and to support the provider. Identification of patient engagement issues and possible measures of treatment outcomes would be generated. Tracking of key patient measures will be facilitated by peripherals enabled to gather objective data such as blood glucose, blood pressure, daily activity, oximetry, and weight [77].The computational process will begin and continue throughout the study process as data are collected, and the patient status is defined by analyzing key health data to form both the initial and updated individual DT using a biopsychosocial framework.Collect deidentified data that will further refine the algorithms used to create the DT and future DTs.

The NCDs that account for the most common cause of death in the United States are cardiovascular disease, cancer, chronic respiratory diseases, and type II diabetes [78]. All of these NCDs are directly influenced by maladaptive behavioral lifestyles such as poor diet, insufficient levels of activity, cigarette smoking, metabolic disorders, and medical conditions, including hypertension and hypercholesterolemia [24]. Biopsychosocial risk factors for the NCDs can include the following items listed in Textbox 1.

Textbox 1.Biopsychosocial risk factors for noncommunicable diseases.
**Genetics**
Metabolic risk factors
**Behavior**
SmokingExcessive alcohol intakeUnhealthy dietLow levels of activity
**Environment**
Air pollutionExposure to carcinogens and toxic wastesTemperature extremesCivic infrastructure
**Demographics**
Access to health careIncome
Age/gender
Ethnicity

### Barriers to Progress and DT Treatment Planning

Effective treatment requires an understanding of barriers to goals, including environmental and demographic factors. Genetics is known to play a role in NCDs, but with personal feedback and targeted treatment, the genetic impact can be mitigated.

We have previously reported on our patient engagement platform that has been used in detecting and treating risk factors for NCDs, including diabetes and chronic pain (MobileNetrix) [79-81,82]. We have also reported on the ability of our patient engagement platform to identify psychological traits that can impact compliance with treatment recommendations and comprehensive care [83]. The patient-facing app is customizable for conditions being studied and is easily adapted to the treatment of all types of NCDs. The app is designed to reinforce patient engagement with their provider, as well as promote behavioral change through automated motivational messaging and psychological principles of change. It can also track patient progress and easily incorporate peripherals and wearables that will provide the needed data to construct a patient-specific DT [84,85]. The programming flowchart for an NCD DT is illustrated in Figure 3. A more detailed explanation of each element is presented in Figure 4.

**Figure 3. F3:**
[figure not shown]
Digital twin overview. DT: digital twin.

**Figure 4. F4:**
[figure not shown]
Overview of inputs and information flow needed to construct a DT for NCDs. AI: artificial intelligence; EMR: electronic medical record; *ICD-10*: *International Statistical Classification of Diseases, Tenth Revision*; NCD: noncommunicable disease.

Biological systems are nonlinear. As noted above, the clinical course of an individual is also usually nonlinear, characterized by many deltas in an EOC toward achieving a treatment goal. Any DT must allow for this variability and continually track the individual through efficient data collection and updating of the DT. Our model for a DT will have 4 essential components. These four components will include (1) the identified patient, (2) the unique model of the patient or DT, (3) rapid and timely synchronized data exchange between the individual and the DT, and (4) ongoing analysis of potential variables that are predictive at a macro level. Using a back-and-forth process and a large number of variables, updates of DTs can include an analysis of all the original variables, including their potential relationships and impact. The DT platform consists of the use of the nearly ubiquitous smartphone that will provide patient-facing data collection and biometric and health data from wearables (eg, Google Fit and Apple Health) and a communication portal with 2-way messaging. A DT Health Management App for both iOS and Android platforms that will be HIPAA (Health Insurance Portability and Accountability Act)-compliant will offer electronic medical record integration, enhanced data entry features, Bluetooth-enabled device syncing (eg, glucose monitors), and emergency alerts. This app will be designed to be robust, scalable, and secure, ensuring seamless integration of various components to deliver a comprehensive health care solution. A custom application programming interface (API) will facilitate secure and efficient data exchange between the mobile app, backend infrastructure, and web portals. An administrative portal will be used by the treating provider to access data with electronic medical record integration and offer decision support, and a super-admin portal will monitor system performance and the computational analysis that supports DT construction and updates. A collaborative information model has been proposed that will be able to evaluate complex systems with multiple inputs interacting together to define a specific outcome [45]. When data to construct or update a DT is incomplete, expert knowledge–based evidence will be used. Figure 3 details DT functioning and data processing, flow, and provider supervision. Table S1 in Multimedia Appendix 1 illustrates communication processes and their APIs.

### Study Objectives

The goal of this study and the primary objective is validation of our automated patient engagement programs to guide participants toward activity gains, sustainability, opinions of the situational relevance of the engagement tools, and other key performance indicators using a DT. The research plan has several objectives. It will examine the impact that personalized health care messaging and treatment recommendations can have on individuals. Secondary objectives include (1) testing published guidelines on a heterogeneous population, (2) developing a methodology that combines multiple different biopsychosocial characteristics into a personalized treatment plan that improves on and is responsive to an individual’s unique background, and (3) refining algorithms that support clinical decision-making of a clinician.

## Methods

### Validation Methodology for a DT NCD

This proposed study will use the smartphone (iOS and Android) and MobileNetrix as the health management systems platform for a patient DT NCD study. A HIPAA-compliant DT Health Management App will be created, supported by AI and computational analysis. The administrative portal will automatically poll each participant after being identified as a candidate based on validated criteria of having one of the NCDs studied in this protocol. The 3 NCDs that will be included are (1) cardiovascular disease, (2) type II diabetes (non–insulin dependent), and (3) chronic obstructive pulmonary disease.

Candidates will be screened through a 2-step evaluation process. After informed consent is received, the participants will be invited to download the study app. Following a successful app enrollment, a screening questionnaire specific to the provisional diagnosis will be sent through the study app that will contain a link to a designated questionnaire. Once complete, if the individual is found to qualify for the study through the screening questionnaire, an appointment will be made for a comprehensive evaluation to confirm the diagnosis and related risk factors. Table 3 details the screening process for each NCD.

**Table 3. T3:** Screening process for specific noncommunicable diseases.

NCD^a^ diagnosis	Screening questionnaire	Confirmatory evaluation
Cardiovascular disease	AHA PREVENT^b^ risk calculator [86]	Laboratory and physical exam: diabetes (%), current smoking (%), mean total cholesterol (mg/dL), mean systolic blood pressure (mm Hg) [87]
Type II diabetes	Diabetes Risk Score Questionnaire [88]	Fasting blood glucose >126 mg/dL, 2-hour OTT^c^ blood glucose >200 mg/dL, HbA_1C_^d^>6.5% [89,90]
COPD^e^	CDQ^f^ questionnaire [91]	Postbronchodilator spirometry ratio of FEV_1_/FVC^g^ of less than 0.70 confirms the presence of persistent airway obstruction and COPD [92]

a Noncommunicable disease.

b American Heart Association Predicting Risk of Cardiovascular Disease Events

c Oral tolerance test.

d Hemoglobin A1C.

e Chronic obstructive pulmonary disease.

f COPD diagnostic questionnaire.

g FEV_1_/FVC: forced expiratory volume in 1 second to forced vital capacity.

If the risk factors are confirmed, an additional evaluation will be used to determine other specific risk factors associated with that condition, including level of physical activity, psychological traits or maladaptive behaviors, and barriers to improvement, including the presence of pain, sleep disruption, smoking, and other comorbidities related to worsening health. For an overview of these inputs, refer to Table S2 in Multimedia Appendix 1. These secondary domains will become the individual’s study-specific targets. All of these factors will be incorporated into the participant’s DT. The DT will be shared with the patient through the study app and reviewed with the patient during an in-person follow-up visit. The study platform will provide daily questionnaires that are specific to each NCD category and problem list. Objective tracking of the patient’s activity level and physiological measures (such as blood pressure, glucose levels, and pulse oximetry) will continue throughout the treatment period. All these daily data points will be used to update the DT and will appear in the participant’s study portal that is part of the patient-facing app. The updated DT primary endpoint will reflect the change in health risk. Participants found not to be compliant with the program will be contacted and interviewed regarding barriers and their impressions of the program. Clinician decision-making will also be tracked. Variance from DT treatment recommendations and the impact on NCD risk factors will be reviewed and statistically compared to expected outcomes from relevant evidence-based literature.

Automated contextual daily motivational messaging that aligns with the participant’s behavioral traits will continue throughout the study period. Daily compliance reminders for medication regimens will be incorporated into the study app. The program goal will be a 37% reduction in long-term health risk from baseline as determined by the NCD-specific risk questionnaire (Tables S1 in Multimedia Appendix 1). This is considered to be a meaningful reduction in health risk using the financial modeling included in this reference that will sustain a DT program [93]. The number of participants in each arm reaching this goal will be used to evaluate the primary objective of this study as noted above. Each candidate will be followed for 6 months, and the study length will be determined by enrollment rate.

The program’s daily questionnaire options include (1) the participant’s impression of the program and global impressions of change, (2) Global Activity Limitation Index, (3) Brief Pain Inventory, (4) medication adherence and compliance, (5) daily diet summary, (6) quality of sleep, and (7) smoking and alcohol consumption.

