#### Enrollment Procedures

The smartphone will be used to communicate with the eligible participants. They will be sent a poll using an SMS text messaging–based survey app for eligibility for in-person evaluation. The administrative portal will automatically categorize participants into a defined level of risk of their NCD. The participants with confirmed NCDs will be evaluated by the interdisciplinary team noted above, and a personal treatment regimen will be designed for them to reduce their health risks, along with a DT that reflects their state of health at enrollment. There will also be a comparison-matched group of participants who will be randomized to a treatment-as-usual condition, where they will not have access to the DT technology. After sufficient instruction, the participants in the experimental treatment condition will be tracked daily and be provided with reinforcing messaging and automated problem-solving based on their DT. Any changes in their health-related behaviors will automatically be reflected in an updated DT. Efficacy of the DT and personalized medicine approach will be measured by the number of individuals reaching a 37% risk reduction, with comparison between enhanced care using the DT and treatment as usual (TAU). TAU is defined as the treatment of one of the study’s NCDs using published guidelines and literature as a guide, but without using any of the DT study interventions. Secondary outcome measures that will be tracked will include each of the diagnosed NCD risk factors and other outcome measures, including compliance and helpfulness ratings of the participants and treating providers. In addition to studying the 3 NCDs noted above, we will select patients diagnosed with type II diabetes with pain for further in-depth analysis, as detailed in the Statistical Methods section.

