Responder rates will be compared between treatment groups using logistic regression. Missing outcomes due to study withdrawal will be treated as nonresponders. The dependent variable in the model will be a binary variable indicating whether the participant was a responder or nonresponder. The model includes treatment assignment as an independent variable and baseline pain severity (Brief Pain Inventory average pain item) as a covariate. An interaction term between treatment and baseline pain sensitivity will be added for subgroup analyses of responder rates.

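### The health-risk endpoint is described in two unreconciled ways, one carried by a digital twin that the control arm lacks, and no common assessment time is fixed for the 37% count

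*Protocol article*

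**What the plan says.** All references are to the protocol article.

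**Validation Methodology for a DT NCD.** Daily questionnaires and objective tracking (activity and physiological measures) feed the DT: "All these daily data points will be used to update the DT". The section then states: "The updated DT primary endpoint will reflect the change in health risk".

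The following paragraph gives a different account: "The program goal will be a 37% reduction in long-term health risk from baseline as determined by the NCD-specific risk questionnaire". It cites Tables S1 of Multimedia Appendix 1 for this. The number of participants in each arm who reach the goal is to evaluate the primary objective. Follow-up is 6 months per person.

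**Enrollment Procedures.** The count reaching 37% is the efficacy comparison of DT with TAU. Of TAU participants the section says "they will not have access to the DT technology", and TAU is defined as excluding all DT study interventions. By contrast, "the participants in the experimental treatment condition will be tracked daily".

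**Table 3.** Three disease-specific questionnaires are named, all in the screening column: the AHA PREVENT risk calculator (cardiovascular disease), the Diabetes Risk Score Questionnaire (type II diabetes) and the CDQ (COPD). A footnote expands the last as "COPD diagnostic questionnaire". A confirmatory evaluation by laboratory tests, examination or spirometry follows.

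**Barriers to Progress and DT Treatment Planning.** Table S1 of the same appendix is described as illustrating communication processes and application programming interfaces.

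**The concern.** A between-arm comparison of responders needs the same quantity, from the same source, at the same time in both arms. The article makes the 37% count its efficacy comparison but describes the underlying risk measure in two ways. One is the DT itself, which only the experimental arm has.

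If the study team applied the DT wording, two things would follow. Risk in the DT arm would come from daily app data while risk in TAU came from something else. The tool under validation would also supply the outcome by which it is validated. A difference between arms could then reflect the measurement and not the patients.

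The questionnaire wording would avoid this, but the article does not say which questionnaire it means. The one pointer to it conflicts with another description of the same table, and no visit is stated at which the 37% is judged. A risk score not collected in TAU at the right time cannot be recovered later, so the matter has to be settled before enrolment.

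**Working it through.** This is a check of text against text. No figure in the article sizes the problem.

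**1. The article's own sample-size figure does not concern this endpoint.** Statistical Methods plans 100 participants on the Patient Global Impression of Change (PGIC) at 3 months: difference 0.6, SD 1.0, 85% power, two-sided 0.05. With n per arm = 2(1.960 + 1.036)² × 1.0² / 0.6² = 17.95 / 0.36 = 49.9, this gives 50 per arm and 100 in total, so the figure reproduces. No control rate, power or sample size is given for the 37% count. The 37% itself rests on a cited source that is not at hand, so it cannot be recomputed.

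**2. The source of the risk measure.**

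| Account | Fed by | Available in TAU? |
|---|---|---|
| Updated DT (Validation Methodology) | Daily app questionnaires and tracking | No: Enrollment Procedures gives TAU no DT access and no DT interventions |
| Disease-specific risk questionnaire (same section, next paragraph) | Unnamed instrument, change from baseline | Not stated; the count is to be made in each arm |

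The first sentence uses the term primary endpoint. The second is the basis of the primary objective. Neither refers to the other or is marked as governing.

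**3. Which questionnaire.** The citation is to Tables S1, but Table S1 is described under Barriers to Progress and DT Treatment Planning as showing communication processes and interfaces. Both descriptions cannot be complete. Other instruments are named in the list of daily questionnaire options and in Statistical Methods (for example the Brief Pain Inventory, painDETECT and the Pain Catastrophizing Scale), but none is a long-term health-risk score. The only disease-specific risk or diagnostic questionnaires named are the Table 3 screening tools. If these are the intended outcome measures, the COPD tool is by its own label diagnostic. It is given to people whose COPD is then confirmed by spirometry, so a fall in its score would not be a fall in long-term risk. The cardiovascular tool is labelled a risk calculator, so this objection does not carry over to it in the same form.

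**4. When.**

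| Place | Time given | For what |
|---|---|---|
| Validation Methodology | 6 months | Follow-up of each candidate |
| Statistical Methods | Baseline and 3 months | Efficacy measures; PGIC at 3 months only |
| Results | 1 year | Active phase of patient tracking |

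None of these is attached to the 37% count, which is worded only as the number reaching the goal.

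**The case against.** The strongest reply is that the only sentence saying how the 37% is determined names a questionnaire and a change from baseline, and the next says that achievers are counted in each arm. On that reading the DT sentence merely describes what the twin displays. This stands in part: the article does not say that the 37% is read from the DT. But the DT sentence uses the term primary endpoint, and nothing subordinates it to the questionnaire.

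Second, the instrument may be specified in the appendix, which is not shown, and an article may leave visit schedules to the full protocol. That is fair as to missing detail. It does not answer the conflict between two descriptions of Table S1, or the two accounts of the endpoint.

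Third, all candidates complete a screening questionnaire through the app before treatment begins, so one questionnaire could be repeated in both arms. It could. The article neither says so nor excludes it.

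It might also be argued that Statistical Methods fixes 3 months for all efficacy measures but PGIC. That sentence closes a list of pain and psychological instruments. The risk questionnaire is not in the list, and the section defining the 37% goal gives 6 months.

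Three stronger readings are tempting, and the documents do not support them:

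- **Repeated chances to cross.** A reader might infer that the DT arm can cross 37% on any of many daily readings. No passage says that crossing at any time counts, and no risk score is among the listed daily questionnaires. A crossing rate would need a mean, SDs and a number of readings that the article does not give.
- **Missing data.** A reader might add that "Missing outcomes due to study withdrawal will be treated as nonresponders" shifts the 37% rates if retention differs. That rule belongs to a model adjusted for baseline pain severity and is not linked to the 37% goal. Neither the size nor the direction of any differential loss is given, and Statistical Methods already plans to compare missing data between groups.
- **Table 3 tools as outcomes.** No passage says that the screening questionnaires are the outcome measures. The COPD point is conditional on that.

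**Conclusion.** The point holds in limited form. The article gives two unreconciled descriptions of the health-risk endpoint, one of which cannot be applied in TAU. It leaves the questionnaire unnamed behind a citation that conflicts with its own text, and it fixes no common assessment time for the 37% count.

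The consequence is conditional. If the DT wording is followed, the arms are measured from different sources and the DT grades itself. If the questionnaire wording is followed, with one suitable instrument at one common visit, the problem disappears. A reader might conclude that the arms are certain to be measured differently; the text permits that but does not state it.

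The size of any bias cannot be computed, because the article gives no responder rate, no distribution of risk change and no reading schedule for this endpoint. The case for acting is that the ambiguity touches the efficacy comparison, is cheap to remove now, and cannot be repaired once TAU follow-up has passed without the needed score. The correction should be made before enrolment.

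**What to change.** 1. Define the 37% responder once, identically in both arms: a fall of at least 37% from baseline on one named questionnaire per disease, scored at baseline and at one fixed visit.
2. For each of the three diseases, name a questionnaire suitable for people who already have the diagnosis, and score it without DT output or app readings.
3. Remove or reword the sentence on the updated DT primary endpoint, so that DT-derived risk is a process measure of the DT arm only.
4. Correct the Tables S1 citation, or the other description of that table.

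The cost is protocol wording plus one scheduled risk questionnaire in TAU. The real concession is that daily DT data no longer count as evidence of efficacy. They remain available to describe engagement and the behaviour of the DT.

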#### Statistical Methods

We expect that both groups (DT Experimental and TAU Control) will have missing data. We will assess whether missing data are more prevalent in one group or the other, and if there are differences among those who drop out early and those who complete the 6-month trial. We will also use corrections for multiple comparisons to reduce the likelihood of type I error (Benjamini-Hochberg correction). A calculation will be produced to determine whether the significance value to interpret statistical significance needs to be different from the standard *P<*.05. Power calculations, as outlined by Cohen [94], will be performed to determine the probability of detecting clinically significant differences between treatment conditions in the primary area of measurement. These calculations will assume a 2-tailed test and α level of .05 that use of a DT will improve activity interference on the activity subscale of the Brief Pain Inventory. The Brief Pain Inventory was chosen as a primary outcome measure. This is because persistent pain and other symptoms are often associated with NCDs that can adversely affect quality of life. The Brief Pain Inventory includes 7 items that assess the degree to which pain and other symptoms interfere with daily living and activity, including general activity, walking ability, normal work (both outside the home and housework), relations with others, sleep, mood, and enjoyment in life (0=does not interfere; 10=completely interferes). These items can be collapsed and averaged into one measure of interference.

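### Lapsed DT participants get a study contact that has no described TAU counterpart, while withdrawal in either arm is scored as failure, so unequal retention could pass for benefit

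*Protocol article*

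**What the plan says.** In Validation Methodology for a DT NCD, the article provides that "Participants found not to be compliant with the program will be contacted and interviewed regarding barriers and their impressions of the program".

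Enrollment Procedures shows which arm this can concern. There, "the participants in the experimental treatment condition will be tracked daily and be provided with reinforcing messaging and automated problem-solving based on their DT". The comparison group is "randomized to a treatment-as-usual condition, where they will not have access to the DT technology", and TAU is defined as guideline-based treatment "but without using any of the DT study interventions".

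The same section says that "Efficacy of the DT and personalized medicine approach will be measured by the number of individuals reaching a 37% risk reduction", compared between DT and TAU. Statistical Methods compares responder rates by logistic regression and adds: "Missing outcomes due to study withdrawal will be treated as nonresponders". For PGIC, that section assigns a score of 1, the bottom of the 7-point scale. The printed condition is that 3-month data exist, which makes sense only if a negative has been lost.

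On missing data in general, the article says "We will assess whether missing data are more prevalent in one group or the other". It also plans a jump-to-reference multiple imputation as a sensitivity analysis, specified for the MMRM.

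**The concern.** A TAU participant has no program to fall out of compliance with and none to give impressions of. As described, the contact can therefore reach only DT participants. An interview about barriers is not labelled a retention step, but it may keep some people in the study who would otherwise have left.

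The scoring rules then convert retention into efficacy. A DT participant who stays because of the contact supplies a real outcome. A TAU participant with the same clinical course who drifts away is counted as a nonresponder and, on the evident reading of the PGIC rule, receives the worst score. Any resulting difference favours DT even if the DT does nothing for health risk. Comparing missingness between arms would reveal such an imbalance but would neither prevent nor correct it.

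**Working it through.** **The plan's own figure.** Inputs from Statistical Methods: PGIC difference 0.6, SD 1.0, two-sided 0.05, 85% power, 15% dropout, equal allocation. The normal-approximation formula gives n per arm = 2 × (1.960 + 1.036)² × 1.0² / 0.6² = 49.9, so 50 per arm and 100 in total, as stated. Recruiting 115 gives about 57.5 per arm.

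**Assumptions, because the article gives no figures.** There is no true effect. Dropout averages the plan's 15% but is split unequally: d1 in DT and d0 in TAU. Completers have mean PGIC 4 and SD 1.0. The extra fraction retained in DT, d0 − d1, has mean PGIC r and SD 1.0. Missing PGIC is scored 1.

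**PGIC.** False difference = (d0 − d1) × (r − 1). SE = √[(V1 + V0)/57.5], where V1 and V0 are the DT and TAU variances of the mixture of completers, retained non-compliers (DT only) and scores of 1. For 10% against 20%:

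- r = 4 (retained people score like other completers): 0.10 × 3 = 0.30; V1 = 1.71, V0 = 2.24; SE 0.262; rejection about 21%.
- r = 3: 0.10 × 2 = 0.20; V1 = 1.74, V0 = 2.24; SE 0.263; about 12%.
- r = 2: 0.10 × 1 = 0.10; V1 = 1.95, V0 = 2.24; SE 0.270; about 7%.

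A wider split of 5% against 25% gives:

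- r = 4: 0.60 points, equal to the whole design effect; SE 0.258; about 64%.
- r = 3: 0.40 points; SE 0.261; about 33%.
- r = 2: 0.20 points; SE 0.275; about 11%.

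With 15% in both arms the difference is 0 and the rate is 5%. A simulation with r = 4 and scores rounded to the 1 to 7 scale gave 20% and 62% for the two splits, in line with these approximations.

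**Responders.** False difference = (d0 − d1) × the response rate among those retained. The test is an exact enumeration of a two-sided 5% two-proportion z test with 58 DT and 57 TAU, standing in for the planned logistic regression.

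If retained people respond like other completers, at 30%, 50% or 70%:

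- 10% against 20%: differences of 3, 5 and 7 percentage points; false positives 6.6%, 9.1% and 12.8%.
- 5% against 25%: differences of 6, 10 and 14 points; false positives 11.5%, 20.3% and 35.0%.
- 15% in both arms: 5.0% to 5.5%.

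If completers respond at 50% but retained non-compliers at only 20%, the differences are 0.10 × 0.20 = 2 points and 0.20 × 0.20 = 4 points. The false-positive rates fall to 6.0% and 7.7%.

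**The case against.** Several points on the other side have force.

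- **What the text says.** It mentions no telephone call, no timing and no retention purpose, and no sentence says TAU participants will be left alone. The Discussion refers to close follow-up of study participants and to incentives without naming an arm. A reader might infer that lapsing TAU participants get nothing; the article supports only that no parallel contact is described.
- **Lapsing is not withdrawing.** The trigger is non-compliance with the program, whereas the failure rule covers withdrawal from the study. Outcome instruments are delivered through REDCap, so someone can stop using the app and still give a 3-month score. The link from interview to retention is plausible but undocumented.
- **The interview may belong to the DT package.** The DT design includes identifying engagement problems, and the primary objective concerns the engagement programs. Contact that is part of the intervention is a legitimate difference between arms. This stands, and it is why the interviews need not be moved or dropped. It does not justify unequal pursuit of outcome data.
- **Size and direction.** A reader might infer that the interview would create the whole 0.6-point design effect. That needs a 20-point dropout gap and retained non-compliers who score as well as everyone else; neither is supported. The article reports minimal attrition in previous work, and the daily questionnaire burden could raise DT dropout instead.
- **Existing safeguards.** The PGIC route depends on correcting a misprint. Without the score-1 rule, the PGIC bias computed here disappears under the same assumptions. With it, every missing PGIC is filled, so jump-to-reference has nothing left to impute for that endpoint. The responder rule is explicit and has no stated sensitivity analysis.

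**Conclusion.** The concern holds as a risk, not as a demonstrated bias. The described contact can reach only the DT arm, and the responder rule scores withdrawal as failure in both arms. If the contact improves DT retention, part of the DT-TAU difference would be retention. That DT is the only arm contacted is a strong inference from the two Methods sections, not a statement in the article.

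The size is unknown. At an assumed 10% against 20% dropout with no true effect, PGIC would shift by about 0.10 to 0.30 points, with roughly 7% to 21% false positives; this also requires the corrected reading of the PGIC rule. The responder false-positive rate at that split is about 6% to 13% over the rates tried. Larger figures need a wider split that nothing in the article supports. The point merits a cheap clarification before recruitment, which the article expects by June 2026.

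**What to change.** Add to Validation Methodology for a DT NCD, after the sentence on non-compliant participants: *Missed outcome assessments at 3 months and at the 6-month risk assessment are followed up in both arms with the same trigger, number of attempts and script. This follow-up is separate from any DT program contact. Outcomes are also sought from DT participants who stop using the app.*

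If the barrier interviews stay within the treatment period, declare them part of the DT intervention so that the comparison is understood to include them.

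Add to Statistical Methods a sensitivity analysis of responder rates that does not score withdrawal as failure, for example multiple imputation of the missing outcome. Correct the condition in the PGIC assignment rule so that its intent is clear.

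The cost is a small amount of reminder work for about 57 TAU participants and one additional analysis.
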